### Randomization and allocation concealment

2.5

In the present study, the 80 recruited patients were divided into FSN and acupuncture groups at a ratio of 1:1. A statistical expert not involved in the design of the study used R Package v3.4.4 to generate a set of random sequences, to be sealed in opaque envelopes prepared in advance. Only FSN and acupuncture practitioners were authorized to open the envelopes to obtain each grouping code.

### Single-blinding

2.6

FSN and acupuncture practitioners were not provided details of treatment plans or grouping information within the envelope in advance. No participant or relevant medical personnel was authorized to interfere with individual treatment selections. Evaluators are blinded to the treatment each patient has received, their function being to assist each patient in completion of the various questionnaires and scoring the respective scales. It is intended that the independent biostatisticians are also blinded when conducting the statistical analysis.

### Discontinuation criteria

2.7

Any serious adverse reactions or other acute or severe event during the study, preventing continued participation in the study;Subjects requesting to withdraw from the study midway;Patients not cooperating with the treatment plan, preventing valid treatment execution even after repeated explanation by the clinician.Results of those exceeding half of the total course of treatment available for inclusion in the statistical analysis of treatments.

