#### FSN group

2.3.1

*FSN selection*: Disposable floating needles (medium: M) produced by Nanjing Paifu Medical Science and Technology Co., Ltd. were selected for use in this trial. These have passed inspection and have obtained a production license (License no: su Shi Yao Jian Xie Xu 20040104; Registration no: 20152270832).

*Procedure*: The patient is placed in a prone position and the MTrP P1, P2, P3, and P4 ascertained (the four positions determined according to positions causing pain, where P1 and P2 points are at the waist, P3 points at the thigh and P4 points on the calf). The position of needle insertion is 3 to 5 cm below or outside the MTrP. An FSN needle insertion device is required to insert the needle. Insertion of the needle tip is required to be at an oblique angle of 15° to 20° relative to the surface of the skin. The preferable insertion depth of the needle is just beyond the depth of the subcutaneous muscle layer. The thumb, index finger, and middle finger are used to move the upper part of the needle body, lift and pinch the needle handle, and sense the tightness of the muscle as the needle tip moves in response to movement of the fingers. The needle body is then gently and slowly lifted until the needle tip leaves the muscle layer and enters the subcutaneous layer for additional sweeping treatment. The duration of scanning time at each needle entry point is approximately 2 minutes, each position scanned approximately 200 times. The treatment cycle requires 3 weeks, usually once a day for the first 3 days, then 2 days apart, for a total of 12 occasions.

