#### Acupuncture group

2.3.2

*Acupuncture needle selection*: Jiajian brand disposable sterile Acupuncture needles, 0.30 × 40 mm and 0.30 × 75 mm, with a production license no: 20060095. *Procedure*: Acupuncture of the bilateral Shenshu (BL 23), Jiaji (BX-B2), Weizhong (BL 40), and Ashi acupuncture points (irregular). The treatment cycle selected for this study was 3 weeks, usually once per day for the first 3 days, then 2 days apart, for a total of 12 occasions.

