### Statistical analysis

2.11

Since FSN and acupuncture are known to have only minimal risk, implementation of additional safety precautions is not required. Sensitivity analysis will be conducted to determine the impact of incomplete records on the results. Missing data will not be estimated. Statistical analysis will be performed using R package v3.4.4 software. If a Shapiro–Wilk test indicates that the data are normally distributed, a *t* test is appropriate for calculation and comparison of differences between two groups, otherwise a Mann–Whitney *U* test is suitable. A *χ*^2^ or Fisher exact test is relevant for calculation of differences in count data.

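### Section 2.7 admits results to the analysis by amount of treatment completed, which by natural reading leaves out randomised patients who stop at or before session 6 of 12

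*Protocol article*

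**What the plan says.** Section 2.7 (Discontinuation criteria) gives three reasons for discontinuation:

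- a severe event: "Any serious adverse reactions or other acute or severe event during the study, preventing continued participation in the study"
- withdrawal: "Subjects requesting to withdraw from the study midway"
- non-cooperation: "Patients not cooperating with the treatment plan, preventing valid treatment execution even after repeated explanation by the clinician"

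It then adds a rule about the analysis: "Results of those exceeding half of the total course of treatment available for inclusion in the statistical analysis of treatments".

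The length of the course is the same in both arms. Section 2.3.1 says "The treatment cycle requires 3 weeks, usually once a day for the first 3 days, then 2 days apart, for a total of 12 occasions", and section 2.3.2 says "usually once per day for the first 3 days, then 2 days apart, for a total of 12 occasions".

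Two sentences in section 2.11 (Statistical analysis) bear on patients with incomplete data: "Sensitivity analysis will be conducted to determine the impact of incomplete records on the results" and "Missing data will not be estimated". The section does not say which patients the sensitivity analysis covers or how it is done.

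**The concern.** Randomisation makes the arms comparable at the moment of allocation. A rule that then admits patients by how many sessions they went on to have selects on something that happens later and that the treatment may influence. A patient may stop early because the needling is painful, because nothing improves, or because relief comes quickly. The two procedures differ, so the mix of such patients may differ between arms.

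Judgement also enters. Under section 2.5 the practitioners open the allocation envelopes, and under section 2.7 a clinician's repeated explanation precedes a finding of non-cooperation. That clinician may know the allocation. The blinded evaluators described in section 2.6 cannot correct for patients whose results never reach the analysis.

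At stake is the comparison on all three primary outcomes (VAS, JOA and ODI). If 3-week scores are not sought from early stoppers, no later analysis can recover them.

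**Working it through.** **Step 1: the threshold.** Half of 12 sessions is 6. Exceeding half therefore means 7 or more, in both arms.

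**Step 2: who is in and who is out.** The rule turns on the number of sessions, not on the reason for stopping:

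- Stops after 7 or more sessions, for any of the three reasons: results are available for the analysis.
- Stops at or before session 6, for any reason: by natural reading, results are not available. No other section brings these patients back.

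**Step 3: how many this could be.** Section 2.5 has 80 patients allocated 1:1, so 40 per arm. Section 2.4 assumes 10% dropout. If every dropout fell at or below half the course, 80 × 0.9 = 72 would remain, or 36 per arm if losses were even. The document does not say how dropouts divide between arms or around the threshold.

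**Step 4: the size of a possible bias.** The plan gives no figure to reproduce here, and neither an SD nor exclusion rates by arm, so the following are assumed cases. Assume no true treatment effect. Let q be the share excluded in an arm, and s the number of SDs by which excluded patients are worse than the mean of their whole arm. The mean of those kept then shifts by q × s / (1 − q) in the favourable direction. The bias b is the difference between the two arms' shifts.

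For 10% v 0%:

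- s = 0.5: 0.10 × 0.5 / 0.90 = 0.056 SD
- s = 1: 0.10 × 1 / 0.90 = 0.111 SD

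The false-positive rate at two-sided 5% (sidedness is not stated and is assumed) is Φ(b/SE − 1.96) + Φ(−b/SE − 1.96), with SE = √(1/n₁ + 1/n₂) and n = 40 × (1 − q) in each arm. This is a normal approximation with the SD among those kept taken as 1.

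| Excluded, one arm v other | Bias, s = 0.5 | False-positive rate | Bias, s = 1 | False-positive rate |
|---|---|---|---|---|
| 10% v 10% | 0 | 5.0% | 0 | 5.0% |
| 10% v 0% | 0.056 SD | 5.7% | 0.111 SD | 7.7% |
| 15% v 5% | 0.062 SD | 5.8% | 0.124 SD | 8.2% |
| 20% v 0% | 0.125 SD | 8.2% | 0.250 SD | 18.4% |

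Equal numbers protect only if prognosis is also equal. With 10% excluded in each arm, but s = 1 in one and s = 0.5 in the other, the bias is 0.111 − 0.056 ≈ 0.056 SD. If excluded patients are better than average, for instance after quick relief, the sign reverses.

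**Step 5: scale.** With 40 per arm, the difference detectable with 80% power is (1.960 + 0.842) × √(2/40) ≈ 0.63 SD. The 10% v 0% cases amount to 0.056 / 0.63 ≈ 9% and 0.111 / 0.63 ≈ 18% of that.

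**The case against.** - **The sentence does not say that only these patients are analysed.** It closes the discontinuation list and can be read as keeping discontinued patients who passed the halfway point. It is true that the exclusion is inferred. But a threshold for inclusion has no purpose unless those below it are left out, and the generous reading still does not admit patients with 6 or fewer sessions.
- **A reader might infer that everyone who stops for a severe event, withdrawal or non-cooperation is removed.** The document does not support that. Such a patient with 7 or more sessions is kept, so it is also too broad to say that stopping treatment means leaving the trial.
- **Section 2.11 plans a sensitivity analysis for incomplete records.** This stands as mitigation. It does not answer the point, because neither its population nor its method is stated and the same section rules out estimating missing data.
- **Definitions of analysis sets commonly sit in a statistical analysis plan or full protocol, and neither is shown.** This also stands: the article's silence on an as-randomised set is not itself a fault. The point rests on the rule that section 2.7 does state. A full analysis set defined elsewhere would conflict with that rule, so the text needs changing in either case.
- **The bias is hypothetical, and the introduction describes the aim as feasibility and preliminary results.** The size does depend wholly on assumptions, and even exclusions of like patients do no harm. But evenness cannot be checked from the retained patients alone.

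**Conclusion.** The point holds in this form: section 2.7 sets a post-randomisation condition, completion of more than half the course, for results to enter the analysis. By natural reading this leaves out randomised patients who stop at or before session 6. Following it can bias the comparison if exclusions differ between arms in number or prognosis.

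The size and direction are unknown. In the assumed cases the bias runs from zero (equal exclusions, same prognosis) to 0.25 SD (20% v 0%, excluded patients 1 SD worse). The 10% v 0% cases are the more modest illustration, with a false-positive rate of 5.7% to 7.7% instead of 5%. These figures assume no true effect, 40 randomised per arm and a two-sided 5% test. They show what could happen and do not predict what will. The document does not support a claim that the result will be biased, or biased in favour of one arm.

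**What to change.** - In section 2.7, remove the half-course rule as the condition for entering the primary analysis. The discontinuation criteria themselves need no change for this purpose.
- State that patients are analysed in their allocated group regardless of the number of sessions received.
- Seek VAS, JOA and ODI at the already scheduled 3-week assessment from patients who stopped treatment, unless they refuse. VAS should be marked on the same 100-mm scale as in section 2.8.1.1. It cannot be marked by phone, and a verbal rating would be a different measure.
- In section 2.11, say that the sensitivity analysis covers randomised patients with no 3-week outcome, and amend "Missing data will not be estimated" to allow this. Otherwise, analysing patients as randomised conflicts with that sentence for anyone who declines follow-up.
- Keep the more-than-half set (7 or more of 12 sessions) as a secondary per-protocol analysis.

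The cost is a change of wording in two sections and some effort to bring early stoppers back to a visit that already exists. The estimated effect may be slightly diluted, because patients with few sessions are counted.

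### Analysis entry is tied to receiving more than half of the treatment course, and no all-randomised analysis is stated, so the primary comparison is conditioned on treatment received after randomisation

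*Protocol article*

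**What the plan says.** Section 2.7 (Discontinuation criteria) gives three reasons for stopping:

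- "Any serious adverse reactions or other acute or severe event during the study, preventing continued participation in the study"
- "Subjects requesting to withdraw from the study midway"
- "Patients not cooperating with the treatment plan, preventing valid treatment execution even after repeated explanation by the clinician"

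It then closes with a rule on the analysis: "Results of those exceeding half of the total course of treatment available for inclusion in the statistical analysis of treatments".

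The course is fixed in section 2.3.1: "The treatment cycle requires 3 weeks, usually once a day for the first 3 days, then 2 days apart, for a total of 12 occasions". Section 2.3.2 gives the acupuncture arm the same total over the same 3 weeks.

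Section 2.11 (Statistical analysis) adds two sentences on incomplete data: "Sensitivity analysis will be conducted to determine the impact of incomplete records on the results" and "Missing data will not be estimated". The article names no other analysis set. It mentions neither intention-to-treat nor any other analysis that keeps all randomised patients.

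**The concern.** How much treatment a patient receives is known only after randomisation and may itself be a result of the treatment. A threshold on it compares the patients in each arm who got past halfway, and randomisation does not make those two groups comparable.

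Each reason in section 2.7 can act differently in the two arms. The procedures differ: FSN involves about 2 minutes and 200 sweeps per site, while the comparator is conventional needling. Practitioners open the envelopes and deliver the treatment (section 2.5), so they know the allocation when non-cooperation is judged. Blinded evaluators and statisticians (section 2.6) do not protect against selection that has already taken place.

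The rule would apply to all three primary outcomes (VAS, JOA, ODI). If 3-week scores are not sought from early stoppers at the time, they cannot be recovered later.

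**Working it through.** **Step 1. The threshold.** Sections 2.3.1 and 2.3.2 give 12 sessions, and half of 12 is 6. Exceeding half therefore means at least 7 sessions, and 6 or fewer falls outside. If the schedule is read as three daily sessions followed by every second day, sessions fall on days 1, 2, 3, 5, 7, 9, 11, 13, 15, 17, 19 and 21. That is 12 sessions in 21 days, with the 7th on day 11. The finding rests on the session count, not on this calendar.

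**Step 2. Does section 2.11 put early stoppers back?** Take a patient with 6 sessions and complete 3-week scores. This patient has no missing outcome, so the sentence on not estimating missing data does not apply. The sensitivity analysis is aimed at incomplete records. Its method and population are not stated, and nothing says that it covers patients below the threshold. If the patient's 3-week scores are missing, they are not imputed. In neither case does the text restore the patient to the comparison.

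**Step 3. Possible size, on assumed values.** The article gives no SD, early-stopping rate or outcome gap, so it has no figure to reproduce and the following is illustration only.

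From the article: 80 randomised 1:1 (section 2.5), so 40 per arm; significance level 0.05 (section 2.4), taken here as two-sided.

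Assumed: true difference 0; SD 1; a share e1 or e2 of each arm excluded; excluded patients g SD worse than retained ones, with g = 0.5 or 1.0.

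- Removing a share e of an arm makes its retained mean look better by e × g.
- Bias in the difference, in SD units = g × (e2 − e1), in favour of the arm with more exclusions.
- SE = √(1/n1 + 1/n2), with n = 40 × (1 − e).
- Type I error = Φ(bias/SE − 1.96) + Φ(−bias/SE − 1.96).

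| Excluded, arm 1 / arm 2 | Analysed | g | Bias (SD) | Type I error |
|---|---|---|---|---|
| 10% / 10% | 36 / 36 | 0.5 or 1.0 | 0 | 5.0% |
| 5% / 15% | 38 / 34 | 0.5 | 0.05 | 5.5% |
| 5% / 15% | 38 / 34 | 1.0 | 0.10 | 7.1% |
| 0% / 20% | 40 / 32 | 0.5 | 0.10 | 7.1% |
| 0% / 20% | 40 / 32 | 1.0 | 0.20 | 13.5% |

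For the last row, SE = √(1/40 + 1/32) = 0.237 and bias/SE = 0.20/0.237 = 0.843. Then Φ(−1.117) + Φ(−2.803) = 0.132 + 0.003 = 0.135.

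**The case against.** **The sentence may be permissive.** It says that results past the halfway point are available for inclusion and does not say that only those results are used. Placed after the discontinuation list, it may simply keep discontinued patients who got beyond halfway, which is wider than a completers-only set. This stands in part: the exclusion is implied, not written. But an inclusion threshold has no function unless those at or below it are treated differently, and no other analysis set is named.

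**The rest may be in a fuller plan.** Analysis sets are often left to the analysis plan, and the planned sensitivity analysis might cover early stoppers. Silence on analysis sets would not be a finding in a journal article. This article is not silent: it fixes a threshold, and a plan with an all-randomised primary set would have to depart from it. The sensitivity analysis deserves credit, but its scope is not stated.

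**The bias may be nil.** Both arms have the same 12-session course, and if few patients stop early, or equal and similar numbers do, there is no bias. This stands, and it is why no definite size can be claimed.

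**Stronger readings that the article does not support.** A reader might infer that the rule costs more patients than the 10% dropout allowance in section 2.4. Early stoppers may be the very dropouts that the allowance covers, and going from 60 to 80 tolerates a loss of 1 − 60/80 = 25%. A reader might also infer that early recovery would end FSN courses sooner. Recovery is not a listed reason for stopping, and the remark on rapid relief in section 4 concerns mechanism. Much larger type I error figures can be produced by assuming heavier one-sided exclusion or a wider outcome gap, but nothing in the article points to such values.

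**Conclusion.** The point holds as a badly fixed rule. As written, section 2.7 ties entry to the analysis to at least 7 of 12 sessions, and no all-randomised analysis is stated. On the natural reading, the primary comparison is conditioned on exposure after randomisation, delivered by practitioners who know the allocation.

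This rests on reading the threshold as excluding those at or below it. That is an inference, though the only one that gives the sentence a purpose.

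Neither the direction nor the size of bias can be derived from the article. The type I error stays at 5.0% when exclusions are equal and alike, and reaches 5.5% to 13.5% in the unequal scenarios shown. Those figures depend wholly on the assumed exclusion shares and outcome gaps. The article does not support saying that the trial will be biased, or that the bias favours FSN. What it supports is that nothing stated protects the comparison if early stopping differs between the arms.

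**What to change.** Replace the last sentence of section 2.7 with:

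> The primary analysis includes all randomised patients in the arm assigned, whatever the number of sessions received; 3-week VAS, JOA and ODI are sought from every patient who has not withdrawn consent to follow-up. The set with more than half of the sessions is a supportive per-protocol analysis.

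In section 2.11, state that patients with no 3-week outcome are handled in the sensitivity analysis already planned there. This keeps the all-randomised definition consistent with the decision not to estimate missing data.

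The cost is a wording change, week-3 visits for the few early stoppers, and possibly a smaller estimated difference. Visits are needed because the VAS is marked on a 100-mm line (section 2.8.1.1). The sample size of 80 does not have to change for this reason, and no rule on treatment or stopping is altered. The change should be made before the first week-3 assessments fall due.

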### Outcomes

2.8

#### Primary outcomes

2.8.1

##### VAS^[16]^

2.8.1.1

Patients were marked on a 100-mm visual analogue scale prior to and 3 weeks following treatment for assessment of their pain level (from no pain to very severe), which was then recorded by the evaluator.

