### Sample size calculation

2.4

In order to determine the number of participants required for each experimental group, the variability of results in a previously published article^[7]^ was used in the calculation. The main results of the two studies were obtained under similar circumstances. The sample size required for an unpaired *t* test was 60 individuals, including 32 in the FSN group and 28 in the acupuncture group. The calculation was performed using a significance level of .05 (i.e., 5% of type I errors, resulting in a 95% confidence interval) and an absolute error of 5%. Considering a dropout rate of 10%, 80 patients are required to generate 80% of the power, at a significance level of .05.^[15]^

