##### JOA Score^[17]^

2.8.1.2

Clinical symptoms and difficulty in performing tasks of daily living were evaluated according to the therapeutic effects evaluation standard of the Japanese Orthopedics Association (JOA) for lumbago. All scores before and 3 weeks after treatment were recorded and total scores calculated, in accordance with JOA's score for lumbago and leg pain severity.

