##### **ODI**^[18]^

2.8.1.3

Prior to and 3 weeks following treatment, the Oswestry disability index (ODI) of each patient was recorded, principally referring to pain (degree of pain, impact of pain on sleep), single functions (lifting/carrying, sitting, standing, walking) and individual comprehensive functions (daily self-care capability, social activities, travel).

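### VAS, JOA and ODI are all primary and unranked, with no rule for success, so the plan's single 5% type I error and 80% power are not both secured

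*Protocol article*

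**What the plan says.** Under the single heading "Primary outcomes", section 2.8.1 of the protocol article lists three separately numbered measures, each taken before treatment and at 3 weeks:

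- VAS (2.8.1.1): "Patients were marked on a 100-mm visual analogue scale prior to and 3 weeks following treatment".
- JOA (2.8.1.2): "All scores before and 3 weeks after treatment were recorded and total scores calculated".
- ODI (2.8.1.3): "the Oswestry disability index (ODI) of each patient was recorded".

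None is put ahead of the others.

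Section 2.4 sizes the trial for one comparison: "The sample size required for an unpaired *t* test was 60 individuals, including 32 in the FSN group and 28 in the acupuncture group". It names no outcome and gives neither a difference nor a standard deviation. The error rate is stated once: "The calculation was performed using a significance level of .05 (i.e., 5% of type I errors". It then says: "Considering a dropout rate of 10%, 80 patients are required to generate 80% of the power, at a significance level of .05".

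Section 2.11 prescribes a t test or a Mann-Whitney test for measured data, depending on a normality test, and a chi-squared or Fisher test for counts. It gives no significance level, no order of testing, no division of alpha, and no statement of how many primary outcomes must be significant.

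**The concern.** A 5% type I error and 80% power are properties of a decision rule. Section 2.4 claims both for one test, but section 2.8.1 sets up three tests of equal standing, and no rule joins them. Each way of completing the plan has a cost:

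- If any one significant outcome counts as success, the 5% is exceeded unless the three tests are perfectly correlated.
- If all three must be significant, the 5% holds, but the 80% planned for one test does not in general carry over to three.
- If alpha is divided among the three, each test has less power than the sample size assumed.

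The trial's main conclusion, whether FSN does better than acupuncture, rests on this choice. While the choice is open in the protocol, a reader cannot tell what a significant result on one scale and not on the others would mean.

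**Working it through.** **Inputs from the document.** Three primary outcomes (2.8.1). Alpha .05, 80% power, 32 + 28 = 60 for one t test, 10% dropout, 80 patients (2.4). 1:1 allocation (2.5).

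**Assumptions.** Two-sided tests (not stated). Each outcome tested at .05 (inferred, since .05 appears only in 2.4). Equal non-negative correlation r between the three test statistics (not given). The same standardised difference d on all three (not given).

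**1. The plan's own figures.** For one test, 1 - 0.95 = 0.05, so the stated 5% is right for a single outcome. The 60 cannot be reproduced without a difference and SD, so d is solved backwards. The normal approximation gives (1.960 + 0.842) × √(1/32 + 1/28) = 2.802 × 0.2588 = 0.725; the noncentral t distribution gives d = 0.737, used below. Evaluable patients after 10% loss: 80 × 0.90 = 72, or 36 + 36. (Separately, 60/0.90 = 67, not 80, so results are shown for both 60 and 72.)

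**2. Any one of three suffices.** If independent: 1 - 0.95³ = 0.1426. With correlation, and U standard normal:

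1 - E[{Φ((1.96 - √r·U)/√(1-r)) - Φ((-1.96 - √r·U)/√(1-r))}³]

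| r | chance of at least one false positive |
|---|---|
| 0 | 14.3% |
| .3 | 13.6% |
| .5 | 12.5% |
| .7 | 10.9% |
| .8 | 9.8% |
| .9 | 8.4% |
| 1 | 5% |

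**3. All three required.** Type I error cannot exceed 5%; with no effect on any outcome it is 0.01% at r = 0, 0.3% at r = .5 and 1.4% at r = .8. Joint power is E[Φ((m - 1.96 + √r·U)/√(1-r))³], where m = d/√(1/n₁ + 1/n₂):

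- 32 + 28: m = 0.737/0.2588 = 2.85
- 36 + 36: m = 0.737/0.2357 = 3.13

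| evaluable | r = .5 | r = .8 |
|---|---|---|
| 60 | 63% | 70% |
| 72 | 74% | 80% |

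This is a normal approximation and slightly favourable. Matched to the power of the t test, the values are about 61% and 69% (60 evaluable), and 73% and 78% (72 evaluable). With 72 evaluable, joint power passes 80% only at about r = .8 to .9.

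**4. Bonferroni.** .05/3 = .0167 per test. Family-wise error is 4.9% (r = 0), 4.5% (r = .5) and 3.5% (r = .8). By the noncentral t distribution with d = 0.737, power per outcome is 65% at 32 + 28 and 75% at 36 + 36.

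The 72-patient results credit the plan with detecting d = 0.737. If the 80% is instead meant to hold at 72 evaluable, d is 0.670 and power per outcome under Bonferroni is again 65%.

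**The case against.** The strongest objection is that silence is not an any-one rule. A reader might infer that the trial's true type I error is about 10-14%. The document does not support that as a fact: it needs success on any single outcome to be allowed, each test to be run at .05, and a correlation of about .8 or less. None of these is stated. The scales also overlap, since JOA and ODI both include pain, so high correlation is plausible and independence is the least realistic case. This objection stands, and the figures above are conditional for that reason.

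A second objection is that a multiplicity rule often sits in a statistical analysis plan, which is not shown. That is fair as to mechanics, and it means one cannot say that the headline outcome will be chosen after seeing the data. But three co-primary outcomes and a sample size for one unnamed test are fixed in this article. A later alpha split or all-three rule would have to be squared with that sample size.

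A third is that the Introduction describes the aim as exploring feasibility and early results, and no formal superiority hypothesis appears. This lowers the severity. It does not remove the point, because section 2.4 still claims a 5% error and 80% power.

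High correlation does not fully rescue the any-one reading either: the error is still 8.4% at r = .9.

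**Conclusion.** The point holds in conditional form. With three unranked primary outcomes and no decision rule, the type I error and power of the main claim are undetermined. If any one outcome suffices, the family-wise error is 5% to 14.3% over r from 1 to 0. If all three are required, the error is controlled, and joint power is about 63-70% (60 evaluable) or 74-80% (72 evaluable) for r = .5 to .8. At most plausible correlations, one of the two properties stated in section 2.4 therefore fails. The exception is an all-three rule with 72 evaluable patients and correlation at or above roughly .8 to .9. The power figures rest on d = 0.737, which is back-solved and not stated in the document.

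This should be fixed. Given the exploratory aim, it does not rank among defects that would stop the trial.

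**What to change.** Before unblinding:

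- **2.8.1:** name one primary outcome at 3 weeks, for example VAS, and make the other two key secondary outcomes in a stated order. The document gives no ranking, so the choice is the sponsor's.
- **2.4:** state that the sample size refers to that outcome.
- **2.11:** test the primary outcome at two-sided .05, then the other two in the fixed order, each formally only if the one before is significant.

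This secures the stated 5% for the primary outcome and for the ordered sequence. It costs wording in three sections and no extra patients. The downside is that the other two outcomes can no longer carry the primary claim alone. Whether power on the chosen outcome is really 80% cannot be confirmed, because section 2.4 gives no difference or SD for any outcome.

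If the sponsor prefers to keep three primary outcomes, the protocol should say whether one or all must be significant, and restate the power in section 2.4 under that rule.
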